### **3.7.6 Treatment of missing data**

Given that data are collected via the VEMD, we expect rates of data missingness to be low, and thus complete-case analyses are planned.

## **3.8 Analysis of secondary outcomes**

### **3.8.1 Patient delay time (in STEMI and suspected STEMI patients) & prehospital delay time (in STEMI, ACS, and suspected STEMI patients)**

Patient delay time and prehospital delay time will be analysed using mixed effects quantile regression models including random intercepts for LGAs and fixed effects for each period and for the intervention. The effect of the intervention will be presented as the difference in median delay times between intervention and baseline periods and associated 95% CIs, where 95% CIs will be based on bootstrapped samples as described in Geraci[18].

### **3.8.2 Binary outcomes: whether patient delay time $\leq 60$ mins (in STEMI and suspected STEMI patients); whether prehospital delay time $\leq 120$ mins (in STEMI, ACS, and suspected STEMI patients); survival to hospital discharge (in ACS patients); survival to hospital discharge following an out-of-hospital cardiac arrest; acute coronary syndrome emergency department presentations via General Practitioners; calls to EMS for chest pain.**

These binary outcomes will be analysed according to the approach outlined in Section on 3.7.1. Analysis of the survival to hospital discharge following an out-of-hospital cardiac arrest outcome will only include participants who had an out-of-hospital cardiac arrest.

### **3.8.3 Number of Heart Health Checks**

The difference in rates of heart health checks between groups will be estimated by fitting a marginal Poisson regression model via generalized estimating equations with an offset term for the number of adults eligible for Medicare in each LGA, with an independent working correlation structure and Kauermann and Carroll

standard errors. In addition to the term for intervention condition, terms for study period will also be included in the model.

**3.8.4 *Rates of emergency department presentations for acute coronary syndrome; rates of emergency department presentations for unspecified chest pain; calls to EMS for non-chest pain; rates of out-of-hospital cardiac arrests.***

The difference in rates of emergency department presentations for ACS and unspecified chest pain, rates of out-of-hospital cardiac arrests and counts of calls between groups will be estimated by fitting a marginal Poisson regression model via generalized estimating equations with an offset term for the population size of each LGA, with an independent working correlation structure and Kauermann and Carroll standard errors. In addition to the term for intervention condition, terms for study period will also be included in the model; such terms will incorporate adjustment for seasonality.

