### Benefits of community cardiovascular risk assessments

ACS is associated with modifiable risk factors that are now common in the Australian community (e.g. high blood pressure, high blood cholesterol, smoking, diabetes, overweight/obesity, and physical inactivity). Community risk screening interventions typically involve assessing members with no known ACS and referring patients identified “at potential risk” to their general practitioners (GPs) for further screening and management. Published studies of public screenings have found high rates of new identified risk factors (in as many as 66% of people screened), and is associated with improved outcomes if subsequently treated. Public screening and referral to GPs are now supported within the Australian health care system, with the Federal Government’s recent implementation of a Medicare item for GPs to conduct Heart Health Checks in adults aged over 45 years (35 years for Indigenous Australians).

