### *Study setting*

The study will be undertaken in eight LGAs in Victoria (3 in greater Melbourne and 5 in regional Victoria).

These LGAs were selected from the list of the 16 highest-risk Victorian LGAs (highest ranking for age-standardised rates of heart attacks) generated from the Victorian Heart Maps.

These LGAs were selected to meet the study's sample size requirements based on admission rates for ACS from the Victorian Emergency Medicine Dataset (VEMD). Estimates, from the 2013-2015 VEMD data, suggests 1,635 ACS events occur in these LGAs annually (annual range across LGAs=102 to 360).

*Table 1. Profiles of the 8 LGAs to be targeted (\*SED= Index of Relative Socio-economic Disadvantage).*

| LGA name | Area km2 | Residents | Index SED* | Median age | Males (%) | Born overseas (%) |
|----------|----------|-----------|------------|------------|-----------|-------------------|
| LGA1     | 489      | 207058    | 991        | 34         | 50        | 36%               |
| LGA2     | 503      | 207041    | 947        | 33         | 50        | 36%               |
| LGA3     | 31       | 86942     | 995        | 34         | 51        | 40%               |
| LGA4     | 2999     | 112267    | 981        | 38         | 49        | 8%                |
| LGA5     | 22082    | 54658     | 935        | 40         | 50        | 11%               |
| LGA6     | 432      | 40100     | 977        | 36         | 50        | 10%               |
| LGA7     | 4518     | 37595     | 967        | 45         | 50        | 7%                |
| LGA8     | 120.7    | 33655     | 986        | 40         | 50        | 8%                |

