## 2.5 Outcomes

Outcomes will be examined for adult (aged 18 years or older) residents of the eight LGAs. All outcomes, except survey data, were collected continuously between December 1st 2022 to March 31st 2023 for the main trial and to March 31st 2024 for long-term follow-up. The survey data was collected at three-time points; December 2021-January 2022 (control), August 2022-September 2022 (half-way), April-May 2023 (completion). This Statistical Analysis Plan provides plans for the analysis of the main trial; the analysis of long-term follow-up data will be covered in a subsequent document.

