- Awareness of heart attack/heart disease as the leading cause of death (the proportion who identify heart attack/disease as a leading cause of death in men/women to be compared between groups)
- Awareness of heart disease (cardiovascular) risk factors (the proportion who correctly identify any cardiovascular risk factor as increasing their risk of heart disease to be compared between groups)
- The number of correctly named heart disease (cardiovascular) risk factors (the mean number of correctly named cardiovascular risk factors to be compared between groups)
- Awareness of heart attack signs and symptoms (the proportion aware of any heart attack symptom[7] to be compared between groups)
- The number of correctly named heart attack signs and symptoms (the mean number of correctly named heart attack symptoms[7] to be compared between groups)
- Confidence in knowing how to act (the proportion very confident/confident about what they would do if experiencing a heart attack to be compared between groups)
- EMS use in severe chest pain scenario (the proportion who state they would call EMS to be compared between groups)
- EMS use in chest discomfort scenario (the proportion who state they would call EMS to be compared between groups)

The following will be obtained from Medicare:

- The number of Heart Health Checks (numbers of Medicare claims for Heart Health Checks, items 699/177) by LGA and month. The number of adults eligible for Medicare in each LGA will allow analysis of this as a rate for each LGA in each month.

The following will be obtained from the VEMD:

- Number of ACS emergency department presentations (numbers of ED presentations that have a final ED diagnosis of ACS[10]), by LGA and month. Adult population sizes of LGAs will be obtained from the Australian Bureau of Statistics to allow analysis of this as a rate for each LGA in each month.
- Number of emergency department presentations that are for unspecified chest pain (the number of ED presentations that have a final ED diagnosis of unspecified chest pain[10]), by LGA and month. Adult population sizes of LGAs will be obtained from the Australian Bureau of Statistics to convert this to a rate for each LGA in each month.
- ACS ED presentations via General Practitioners (the proportion of ACS ED presentations referred to ED by General Practitioners to be compared between groups)

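### The Heart Health Check rate is divided by all Medicare-eligible adults although the item starts at 45 (35 for Indigenous Australians), so in this allocation LGA age mix shifts the estimated rate ratio

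*Supplement*

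**What the plan says.** SAP 2.5.2 defines the outcome as "numbers of Medicare claims for Heart Health Checks, items 699/177", counted by LGA and month, and adds: "The number of adults eligible for Medicare in each LGA will allow analysis of this as a rate for each LGA in each month". SAP 3.8.3 carries this into the model as "an offset term for the number of adults eligible for Medicare in each LGA". SAP 2.5 sets the meaning of adult: "Outcomes will be examined for adult (aged 18 years or older) residents of the eight LGAs".

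The amended protocol, under Benefits of community cardiovascular risk assessments, describes a Medicare item for GPs to "conduct Heart Health Checks in adults aged over 45 years (35 years for Indigenous Australians".

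The model in SAP 3.8.3 is a marginal Poisson regression fitted by GEE, "with an independent working correlation structure and Kauermann and Carroll" standard errors. On other covariates it says only: "In addition to the term for intervention condition, terms for study period will also be included in the model". It has no LGA effect and no age term. No age-standardised rate or age-restricted sensitivity analysis is planned for this outcome.

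**The concern.** Most adults below 45 count in the denominator but, on the protocol's description of the item, cannot appear in the numerator. The rate per adult is therefore the uptake among eligible people multiplied by the eligible share of adults, and that share differs between LGAs. Median ages in protocol Table 1 run from 33 to 45.

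A denominator error that is constant within an LGA would cancel if the model compared each LGA with itself. With independence working correlation and no LGA terms, the comparison within each period is between LGAs that have crossed and LGAs that have not. If the LGAs that cross early are older, they show a higher rate per adult whether or not the campaign works.

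Increasing Heart Health Checks is a stated secondary objective, and SAP 3.1.2 reports p-values without multiplicity adjustment. A ratio somewhat above 1 could be read as a campaign effect.

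**Working it through.** The documents give no expected rate, sample size or power for this outcome, so there is no planned figure to reproduce. The check asks what the planned model returns when the campaign does nothing.

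**Inputs**
- Crossing order: protocol Table 4. Transition cells are excluded under SAP 3.2, leaving 8 × 7 = 56 LGA-periods.
- Residents and median age: protocol Table 1, whose rows are labelled LGA1 to LGA8. They are matched to names by the row order of SAP Table 2, which is an inference. All residents stand in for adults as weights.
- Eligible share of adults: not given. Assumed linear in median age between a low value at 33 and a high value at 45. The Indigenous 35-44 group is left out for lack of data.
- Equal check uptake among eligible people in every LGA and period.

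| LGA | Launch | Residents | Median age | Share in the 45-60% scenario |
|---|---|---|---|---|
| Greater Bendigo | T2 | 112,267 | 38 | 0.5125 |
| Campaspe | T2 | 37,595 | 45 | 0.6000 |
| Maribyrnong | T3 | 86,942 | 34 | 0.4625 |
| Wodonga | T4 | 40,100 | 36 | 0.4875 |
| Warrnambool | T5 | 33,655 | 40 | 0.5375 |
| Mildura | T6 | 54,658 | 40 | 0.5375 |
| Whittlesea | T7 | 207,058 | 34 | 0.4625 |
| Hume | T7 | 207,041 | 33 | 0.4500 |

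**Which periods inform the estimate.** With period terms in the model, only periods containing both conditions contribute. T1 and T2 have control cells only; T7 and T8 have intervention cells only. That leaves T3 to T6. In all four, Greater Bendigo and Campaspe are intervention, and Whittlesea and Hume are control.

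**Null ratio by period, 45-60% scenario.** Each rate is Σ(residents × share) / Σ(residents).

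| Period | Intervention cells | Control cells | Ratio |
|---|---|---|---|
| T3 | 80,094 / 149,862 = 0.534 | 255,950 / 542,512 = 0.472 | 1.13 |
| T4 | 120,305 / 236,804 = 0.508 | 236,401 / 502,412 = 0.471 | 1.08 |
| T5 | 139,853 / 276,904 = 0.505 | 218,311 / 468,757 = 0.466 | 1.08 |
| T6 | 157,943 / 310,559 = 0.509 | 188,933 / 414,099 = 0.456 | 1.11 |

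The Poisson fit to the expected counts of all 56 cells combines these into 1.10.

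**All scenarios, and the two remedies**

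| Eligible share across LGAs | Adult offset, as planned | Item-eligible offset | Adult offset plus LGA fixed effects |
|---|---|---|---|
| 48-56% | 1.05 | 1.00 | 1.00 |
| 45-60% | 1.10 | 1.00 | 1.00 |
| 40-65% | 1.18 | 1.00 | 1.00 |

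The item-eligible column is 1.00 by construction, given equal uptake. Other assumed age shapes give similar sizes: 1.14 if ages are uniform from 0 to twice the median, and 1.05 if they are exponential.

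**Over the randomisation.** There are 2 × 4! = 48 allocations that keep the two pairs on the two double sequences. Over these, the null ratio has geometric mean 1.00 in each scenario. It ranges from 0.92 to 1.08 (48-56%) and from 0.86 to 1.16 (45-60%).

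**The case against.** A reader might infer that the analysis is biased in favour of the campaign. The documents do not support that. Sequences were randomised, the null ratio averages 1.00 over the permitted allocations, and another draw would have pushed the estimate below 1. This is chance imbalance in one known allocation. The cluster-robust standard errors also carry between-LGA rate differences, including those due to age, so part of the shift is reflected in the interval width. No effect on coverage or type I error has been shown.

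The imbalance is also smaller than the 33-45 range suggests. Weighted by resident-periods, median age is 37.1 in intervention cells and 34.7 in control cells. Maribyrnong, with a median age of 34 on the same row match, crosses second and supplies about a fifth of the intervention resident-time.

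A corrected offset removes only one LGA difference. If uptake among eligible people varied between LGAs with an assumed SD of 0.1 on the log scale, the null ratio under this allocation would range from about 0.86 to 1.18 (95% range) even with a perfect denominator.

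The age limit rests on one background sentence; SAP 2.5.2 names the items without an age rule. Possibly the SAP's wording was meant as eligible for the item, but it does not say so. Age mix also affects the per-adult rates in SAP 3.8.4, though the documents state no age limit for those outcomes.

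All of this stands, and it limits the claim. It does not justify keeping a denominator that includes people the protocol says the item does not cover, when the mismatch is known in advance and easily removed.

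**Conclusion.** The mismatch between the denominator and the item's population is explicit in the text, and the planned model lets it reach the point estimate. Under the known allocation the expected rate ratio with no campaign effect is about 1.05 to 1.18, above 1 in every scenario tried.

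The direction depends on the inferred match of Table 1 rows to LGA names. The size depends also on assumed eligible shares, on Table 1 residents as weights and on equal uptake among eligible people. It should be read as a range, not an estimate. It is a conditional shift in this trial's result, partly carried by the robust standard errors, and not bias over the randomisation. It concerns one secondary outcome and leaves the primary analysis untouched. The correction is worth making because it is cheap.

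**What to change.** In SAP 2.5.2 and 3.8.3, replace the offset with the LGA population eligible for the item: residents aged 45 and over plus Indigenous residents aged 35-44. Check this against the item's age rule in force during the trial. Take the counts from the Australian Bureau of Statistics, which the SAP already uses for its other population rates, and state the same denominator for the per-1000 rates in SAP Table 5.

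Add a sensitivity analysis of this outcome with LGA fixed effects, since the new offset does not remove other LGA differences in uptake.

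The cost is one population table by age, one further model and the SAP wording. No new trial data are needed.

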**3.8.5 *Analysis of survey outcomes***

Awareness of own risk of heart attack, awareness of heart attack/heart disease as the leading cause of death, awareness of heart disease (cardiovascular) risk factors, awareness of heart attack signs and symptoms, confidence in knowing how to act, EMS use in severe chest pain scenario and EMS use in chest discomfort scenario are all binary outcomes and will be analysed in the same manner as the other binary outcomes obtained from other sources. The average number of correctly named heart disease (cardiovascular) risk factors and the number of correctly named heart attack symptoms will be compared between groups by fitting linear mixed models with random intercepts for local government areas and fixed effects for each period and for the intervention. The Kenward-Roger correction will be applied to adjust for the small number of local government areas.

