### **Stepped wedge trial schematic**

The schematic for the Heart Matters stepped wedge trial is displayed below. It has 6 sequences, where 2 local government areas are assigned to each of the first and last sequences of the trial. Periods are each two months long, with transition periods between control and active implementation periods incorporated in each sequence.

Figure 1. Stepped wedge cluster trial design including baseline, transition, and active implementation periods.

[figure not shown]

LGA: Local Government Area

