## 2.8 Sample size

The stepped wedge design in the schematic (a six-sequence stepped wedge design, with an implementation period and two clusters assigned to the first and last sequences) will give 80% power to detect a change in the proportion of ACS patients in the eight LGAs arriving via EMS by 11%[10, 12] from a baseline of 61% to 72%, with a two-sided significance level of 5%. This detectable difference depends on an average of 40 ACS patients admitted per LGA in each two-month period (i.e. a total of 2240 ACS patients) and on the intra-cluster correlation, estimated to be 0.09 using data from the Victorian Emergency Minimum Dataset (VEMD) (2011-2015). This data indicated that more complex correlation structures, with decaying correlations over time, were unnecessary. The Stepped Wedge Stata Program was used for the sample size calculation,[13] verified using the Shiny CRT app.[14] No adjustment was made for LGA or participant attrition, as health services routinely collect the outcomes.

A sample size calculation was also conducted for two online surveys to determine a change in the level of knowledge of ACS symptoms. An online survey in 2020,[7] showed 25% of adults in the intervention LGAs (20% state-wide) could not name any heart attack symptoms. To detect a change from 25% to 10%, with 80% power and 2-sided significance level, requires a survey of 72 adults in each LGA in months 1-2 and again in months 9-10, assuming an intracluster correlation of 0.1, and a cluster autocorrelation of 0.9.

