#### **3.1.2 Level of statistical significance**

All applicable statistical tests will be 2-sided and will be performed using a 5% significance level. No adjustments for multiplicity will be made. Instead, 95% confidence intervals and p-values will be reported.

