### **3.7.2 Different within-cluster correlation structures**

To assess the impact of the assumption of different within-cluster correlation structures on the estimation of the effect of the education campaign on the primary outcome, the analysis estimating a risk difference in Section 3.7.1 will be repeated assuming a block-exchangeable within-cluster correlation structure, including random effects for cluster and cluster-period.

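### The survey mixed models omit the LGA-by-round variation that the survey was sized for; if the plan's own values hold, those intervals are about 25% too narrow

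*Supplement*

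**What the plan says.** SAP 2.8 sizes the survey on one outcome, the share of adults who cannot name any heart attack symptom. The target is stated as "To detect a change from 25% to 10%, with 80% power and 2-sided significance level". By the plan's calculation this "requires a survey of 72 adults in each LGA in months 1-2 and again in months 9-10". The correlation inputs behind that number are given as "assuming an intracluster correlation of 0.1, and a cluster autocorrelation of 0.9". SAP 2.5 gives the survey schedule: "The survey data was collected at three-time points".

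SAP 3.8.5 covers nine survey outcomes.

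- Two are mean counts (risk factors named, symptoms named). They are compared with "linear mixed models with random intercepts for local government areas and fixed effects for each period and for the intervention", using Kenward-Roger.
- Seven are binary and follow SAP 3.7.1. Each gets a risk difference from an identity-link binomial mixed model with an LGA random intercept. Each also gets an odds ratio from a marginal logistic model fitted by GEE, with an independence working correlation and Kauermann-Carroll standard errors.

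SAP 3.7.2 adds a check for the primary outcome: "the analysis estimating a risk difference in Section 3.7.1 will be repeated assuming a block-exchangeable within-cluster correlation structure". No such check is planned for the survey. The output shells agree: Table 7 has a place for a CAC for the primary outcome, while Table 6 has only an ICC column for the survey outcomes.

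On testing, SAP 3.1.2 says: "All applicable statistical tests will be 2-sided and will be performed using a 5% significance level". It makes no multiplicity adjustment.

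**The concern.** A CAC of 0.9 says that two adults from the same LGA are less alike when surveyed in different rounds than in the same round. That is an extra variance component for each LGA-round. A model with an LGA intercept only has no place for it. It treats the LGA-round means as varying around a fixed LGA level through sampling of individuals alone, and its standard error is too small if the component exists.

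Kenward-Roger does not help, because it corrects for estimating the variance components that are in the model and not for one that is missing.

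Awareness, knowledge and confidence are primary objectives 3 and 4 of the protocol, and every survey outcome is to be reported with a p-value. Understated standard errors would lead to gains in awareness being declared too often. The protocol's own statistical methods section warns that a misspecified within-cluster correlation gives intervals of the wrong width.

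**Working it through.** **Inputs.** From SAP 2.8: m = 72 adults per LGA-round, ICC 0.1, CAC 0.9, 25% to 10%, 80% power. From SAP 3.1.2: two-sided 5%. On the design, the SAP schematic says: "It has 6 sequences, where 2 local government areas are assigned to each of the first and last sequences of the trial". Protocol Table 4 puts the launches at T2, T2, T3, T4, T5, T6, T7, T7. From SAP 3.2: transition data are excluded.

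**Step 1: was the 0.9 really used?** Take two rounds (T1, T5), with 4 LGAs in intervention and 4 in control at T5, on a unit-variance scale.

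- Variance of an LGA-round mean: 0.1 + 0.9/72 = 0.1125.
- Correlation between the two rounds: (0.1 × 0.9)/0.1125 = 0.8.
- Variance of the effect: 0.1125 × (1 − 0.8²) × (1/4 + 1/4) = 0.02025, so the SE is 0.1423.
- Outcome variance averaged over 25% and 10%: (0.1875 + 0.09)/2 = 0.13875, so the SD is 0.3725.
- SE of the difference: 0.1423 × 0.3725 = 0.0530. Then 0.15/0.0530 − 1.96 = 0.87, which gives power of 80.8%.

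Solving for m gives 70. With the variance taken at the mean proportion it gives 75, and power at 72 is 79.2%. Both agree with the stated 72. With CAC = 1 only 40 to 42 adults would be needed, so the 0.9 was used.

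**Step 2: size of the omitted component,** per LGA-round mean.

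- Sampling variance, in the model: (1 − ICC)/m = 0.9/72 = 0.0125.
- LGA-by-round variance, not in the model: ICC × (1 − CAC) = 0.1 × 0.1 = 0.01.

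**Step 3: effect on the standard error.** The intervention effect is estimated almost entirely within LGAs, so

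model SE / true SE = √[0.0125/(0.0125 + 0.01)] = √(0.0125/0.0225) = 0.745.

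Intervals are about 25% too narrow. Type I error is 2 × [1 − Φ(1.96 × 0.745)] = 14.4%.

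**Step 4: checks on the actual schedule,** leaving out the T5-launching LGA in round two where transition data are dropped.

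- Model-based against sandwich variance: ratio 0.75 to 0.76, type I error 13.7% to 14.2%.
- 4,000 simulated REML random-intercept fits with normal outcomes: ratio 0.746 and 14.2% (three rounds); 0.753 and 14.7% (two rounds).
- The same three-round simulation with a true CAC of 1: ratio 0.976 and 5.7%. The excess therefore comes from the omitted term.
- Approximate (Satterthwaite) degrees of freedom in the random-intercept model are about 720 to 1,560. The critical value stays near 1.96, so a degrees-of-freedom correction changes almost nothing.

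**Step 5: other values,** three rounds, m = 72.

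| ICC | CAC | Type I error |
|---|---|---|
| 0.1 | 0.8 | about 22% |
| 0.1 | 0.9 | about 14% |
| 0.1 | 0.95 | about 10% |
| 0.05 | 0.9 | about 9% |
| 0.01-0.02 | 0.9 | about 6-7% |

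**Step 6: the GEE odds ratios.** With simulated binary data at CAC 0.9, the mean Kauermann-Carroll SE is 0.92 of the true SE. Type I error is 10% against the normal and 5.5% against t with 6 degrees of freedom. This is ordinary small-sample behaviour with eight clusters, not the 25% understatement.

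**The case against.** The strongest reply is that the plan does not rest on the random-intercept model alone. Each of the seven binary outcomes also gets a GEE odds ratio whose robust standard error does not assume CAC = 1, and SAP 3.7.1 uses only that estimate if the identity-link model fails to converge. This stands. A reader might infer that the whole survey analysis is affected, and the documents do not support that: for the binary outcomes, one of two planned estimates is at fault. The odds ratio does not mend the risk difference reported beside it with its own interval and p-value, and the two mean-count outcomes have no second estimator.

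A second reply is that ICC 0.1 and CAC 0.9 are assumptions made for one outcome. SAP 2.8 gives no values for the other eight. This also stands: 14% is what the plan's own inputs imply, not a known error rate for every survey outcome.

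A third is that these are not the primary outcome, and the SAP openly makes no multiplicity adjustment. That lowers the severity. It does not make a 95% interval with the wrong width acceptable.

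A reader might also extend the point to the registry and dispatch outcomes in SAP 3.8.2. The SAP assumes no CAC below 1 for any of them. For the primary outcome, SAP 2.8 reports that earlier data gave no need for decaying correlations, and SAP 3.7.2 provides a check anyway.

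**Conclusion.** The inconsistency is real. SAP 2.8 budgets for LGA-by-round variation, and the survey mixed models leave it out. It affects the mean differences of two outcomes and the risk differences of seven.

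The 25% and 14% figures hold if 72 per LGA-round, ICC 0.1 and CAC 0.9 hold. They also rest on a normal approximation, which for the risk differences stands in for the binomial model. The direction is the same for any CAC below 1; the size depends on values that the SAP does not give for most survey outcomes.

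This should be fixed. It does not threaten the primary analysis.

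**What to change.** In SAP 3.8.5, add an LGA-by-round random effect (block-exchangeable structure) to the survey linear mixed models and the survey risk-difference models, with small-sample degrees of freedom. If the identity-link model then fails to converge, fall back on the GEE estimate, as SAP 3.7.1 already provides. Add a CAC to Table 6.

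With this model, 1,500 simulated fits per design give type I error of about 4.5% for three rounds (t, 23 − 8 − 3 = 12 degrees of freedom) and 2.9% for two rounds (t, 15 − 8 − 2 = 5). Against a normal reference they give 6.9% and 8.6%, so the degrees of freedom matter.

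The costs are:

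- standard errors about 1.33 times as large under the planning values;
- one more variance parameter, estimated from about 23 LGA-round cells (8 × 3, less one transition cell), and slightly conservative tests if only two rounds are used;
- some added risk that the identity-link model does not converge.

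Power for 25% to 10% with three rounds is about 82-83% by normal approximation, and somewhat lower with a t reference.

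For the SAP 3.8.2 outcomes, extending the SAP 3.7.2 sensitivity analysis is the most that the documents support.
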